##### Secondary treatment period 2: primary study outcomes after 12 weeks

In evaluating the benefits of continuing treatment during the secondary treatment period, we will use generalized estimating equation (GEE) methodology to account for the correlation among a study participant’s repeated measures. We will look for changes from baseline in our primary outcomes to the longer term time points of interest (i.e., Week 12 and 26). We will also conduct secondary analyses looking at continuous outcomes using change scores from baseline to the time point of interest (i.e., Week 12 and 26). Because Group 1 (the waitlist control) will receive treatment during this period, the analyses will be restricted to Groups 2 through 6. The first model will include all main effects of primary dose (i.e., Group), additional treatment (i.e., Booster), and week as indicator variables:

(2.1)$$\begin{array}{l} \text{logit}\left(Y_{\mathrm{ij}}\right)=\beta_{0}+\beta_{1}Group3_{i}+\cdot \cdot \cdot +\beta_{4}Group6_{i}\\ \;+\beta_{5}Booster_{i}+\gamma_{1}Week26_{\mathrm{ij}}+\alpha Z_{i}\\ \text{for i=1,}..\text{,n and j=1,}2 \end{array}$$

where *Booster*_*i*_ is 1 if study participant *i* is randomized to continue treatment (i.e., 60 min 1×/week for 6 weeks) at week 5 and 0 otherwise, and *Week*26_*ij*_ is 1 if the outcome measurement was taken at Week 26 for study participant *i* at repeated measure *j* and 0 otherwise. In model 2.1 we will also incorporate potential interactions between Group, Booster, and Week, but we will have the most power to test for the main effects for Group and Booster and interactions with Week.

This model framework will allow us to answer certain key questions. For instance, we will be able to determine whether additional treatment beginning at week 5 improves outcomes at later time points (*H*_o_: *β*_5_ = 0) and if this improvement changes from week 12 to week 26 (i.e., a significant interaction between Week and Booster). We would also be able to assess if there are differences between the 5 Groups at week 12 and at week 26 and how these differences change over time. We will have less power to explore which Group by Booster dose is optimal, but we will at least be able to observe trends. This analysis will allow us to evaluate the relationships among Group, Booster treatment, and time. Further analyses will incorporate primary outcome data collected at follow-up time points via mail questionnaires (10, 16, 20, 39 weeks).

In summary, this study design including both the primary and secondary treatment periods, will allow us to assess the effect of different doses of massage, of different treatment durations (4 versus 10 weeks), and how these effects change over time and interact with each other.

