### Randomization to treatment group

A total of 228 participants with neck pain will be randomized (38 to each of the 6 study groups). After collecting baseline data, the Research Specialist will electronically randomize participants to treatment group. Treatment groups will be assigned by a computer-generated sequence of random numbers using a program that ensures that treatment allocation cannot be changed after randomization. Participants will be randomized in blocks of varying size to ensure balanced but unpredictable assignment of participants to all treatment groups. The computer will be programmed to randomize within two strata based on the baseline value of neck dysfunction as measured by the Neck Disability Index (5 to 14 and 15+).

After 4 weeks of treatment, individuals within each of the 5 treatment groups (Groups 2–6) who complete the 5 week outcome assessment will again be randomized, within group, to receive 6 more weekly 60 min sessions or no additional treatment. This will be done using independent block randomization, with stratification by baseline value of neck dysfunction, so that there are approximately equal numbers of participants in each treatment group randomized to additional treatment and to no additional treatment. This second randomization will allow us to evaluate the benefits, if any, of 6 weeks of additional treatment. Because Group 1 (wait list controls) had been promised massage treatment after the waiting period, they will receive weekly 60 min massages for 4 weeks.

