### Statistical issues

#### Sample size and the detectable difference

Our sample was chosen to ensure adequate power to detect a significant difference between at least two of the 5 groups receiving a massage treatment in the first 4 weeks of the trial (and not just adequate power to find a difference between one or more of the treatment groups and the waitlist control group). This reflects the primary goal of the trial: to compare the effects of different doses of massage on neck-related disability, and not just to determine if massage is better than no-additional treatment (as in the waitlist control). Our primary outcome is the binary measure of clinically relevant improvement of at least 5 points on the Neck Disability Index (NDI) at 5 weeks compared to baseline NDI score
[31]. Based on findings in our pilot study, we assumed that 7% of the waitlist control group and 35% of Group 2 (60-min weekly treatment) would improve. We lack pilot data to estimate improvement rates in the other groups. Therefore, to permit sample size estimation, we will assume that treatment benefits will increase with the number of treatments given per week (for a fixed weekly dose) and with the number of minutes of massage per week. We assume a two–fold improvement from the lowest to the highest weekly dose (i.e., 60 to 180 min), based on the expectations of our consultant massage therapists. Table
4 summarizes our assumptions for both the NDI and neck bothersomeness score.

**Table 4 T4:** Assumptions for sample size calculations

**Group**	**Amount of massage (weekly dose)**	**Proportion with clinically relevant improvement on NDI (at least 5 point improvement)**	**Proportion with clinically relevant improvement on Bothersomeness score (≥ 30% improvement)**
1	Waitlist	0.07	0.10
2	60 min 1×/week (60 min)	0.35	0.48
3	30 min 2×/week (60 min)	0.40	0.55
4	60 min 2×/week (120 min)	0.55	0.65
5	30 min 3×/week (90 min)	0.60	0.70
6	60 min 3×/week (180 min)	0.70	0.80

To protect against multiple comparisons, we will use Fisher’s protected least significant difference approach. Although this approach has been shown to inadequately protect against the type I error rate for studies with more than 3 groups,

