[32] we ran several simulations to test the type I error rate for our specific study design of 6 groups, with a binary outcome. We did this for sample sizes ranging from 30 to 40 and assuming an overall baseline improvement rate of either 0.07 or 0.50. We found that the type I error remained below 0.05 for all these situations. Following Fisher’s protected least significant approach, we will first use the omnibus Chi-Square test to test if there is any significant difference between all 6 groups and, if we find one, we will test for pairwise differences between groups. With 34 participants per group, we will have 97% power to find a significant difference between at least two of the 6 groups and 80% power to find a significant difference between Group 6 and Group 2, the treatment groups assumed to differ most in proportion of improvement. Assuming 10% loss to follow-up (as found in our pilot study and in our studies of back pain), we plan to recruit 38 participants in each group, for a total sample size of 228 in the trial.

Our other primary outcome is improvement in the Neck Pain Intensity Score of at least 30% from baseline, which reflects clinically important improvement
[33]. With a final sample size of 34 participants in each group we would have 99% power to find a significant difference between at least two of the 6 groups and 80% power to find a significant difference between Group 6 and Group 2 assuming improvement rates as outlined in Table
4. Therefore, we will have adequate power to assess both our primary outcomes.

It should be noted that both primary outcomes (function and symptoms) will be tested at each time point at the 0.05 level because they address separate scientific questions. Analyses of both outcomes at all follow-up times will be reported, imposing a more stringent requirement than simply reporting a sole significant
[34].

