To address our second aim, the optimal duration of the treatment period, we will assess whether continuing treatment for another 6 weeks (60-min weekly massages for 6 weeks) improves outcomes in Groups 2–6. To simplify the power calculations, we focus on the 12 week response outcome and present those here. For the NDI (as a binary outcome), the power is 81%, when adjusting for group, assuming there are 34 participants in each of the 5 groups and assuming that, compared with those whose treatment stopped at 4 weeks, the additional proportion of each group improving at least 5 points from baseline after receiving 10 weeks of treatment is 0.2. The power is 88% for the binary neck pain intensity outcome, when adjusting for group and assuming that there are 34 patients in each of the 5 groups and assuming that, compared with those whose treatment stopped at 4 weeks, the additional proportion of each group improving at least 30% from baseline after receiving 10 weeks of treatment is 0.2.

Our power calculations are based on simple comparisons of the follow-up scores at a single point in time with adjustment for baseline values using logistic regression. We also plan to adjust for other baseline characteristics (e.g., age, gender). Inclusion of such baseline covariates can improve precision of the variance estimate and therefore increase power. For analyses of follow-up data for weeks 10 through 39 we will use generalized estimating equation methodology to handle within person correlation, possibly increasing our power at a given time point.

In summary, we have excellent power to detect clinically meaningful differences for both primary outcomes at both 5 and 12 weeks.

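### The only covariates named for the booster comparison predate the first randomisation; adding the week-5 score in a separate booster model would gain some precision

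*Protocol article*

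**What the plan says.** All references are to the protocol article.

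- **Who enters the booster comparison (Randomization to treatment group).** Members of Groups 2 to 6 "who complete the 5 week outcome assessment will again be randomized, within group". The second allocation is stratified by baseline neck dysfunction, not by week-5 status.
- **What is measured at week 5 (Primary outcomes; Table 2).** Both co-primary outcomes, NDI and pain intensity.
- **The booster analysis (Secondary treatment period 2, Model 2.1).** "We will look for changes from baseline in our primary outcomes to the longer term time points of interest", namely weeks 12 and 26. The model has Group, Booster, Week and Z, and the booster hypothesis is that β5 is zero. The same model is also meant to compare the five dose groups at weeks 12 and 26.
- **The covariates.** Z is described under Models 1.1 and 1.2 as potential confounders that include the baseline outcome score. It is not redefined for Model 2.1. The sample size section adds age and gender as examples of further baseline characteristics.
- **The planned power (Sample size and the detectable difference).** On function the article states: "For the NDI (as a binary outcome), the power is 81%, when adjusting for group, assuming there are 34 participants in each of the 5" (meaning dose groups). On pain it states: "The power is 88% for the binary neck pain intensity outcome, when adjusting for group". The assumed NDI effect is that "the additional proportion of each group improving at least 5 points from baseline after receiving 10 weeks of treatment is 0.2"; the pain calculation also assumes a 0.2 increase. The section adds: "Our power calculations are based on simple comparisons of the follow-up scores at a single point in time with adjustment for baseline values".

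**The concern.** Model 2.1 serves two randomisations with one covariate vector. For the dose groups, the last measurement before allocation is the original baseline. For the booster it is the week-5 assessment, which already reflects each person's response to the first four weeks. A score taken seven weeks before the week-12 outcome is likely to predict it better than one taken before any treatment.

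The article itself argues that baseline covariates can improve precision and power. By that reasoning the week-5 score is the natural covariate for the booster, but it is not named. At stake is precision for Aim 2, which rests on about 85 v 85 participants (5 groups of 34, split 17 v 17) and is powered for a 20-point difference. If the true effect is smaller, extra precision matters more.

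**Working it through.** **Inputs from the article.** Level 0.05, since "both primary outcomes (function and symptoms) will be tested at each time point at the 0.05 level" (two-sided assumed; sidedness is not stated). 34 per group in five groups, split about 1:1, so n = 17 per arm per group. Rates without booster from Table 4 (week-5 rates assumed to carry to week 12): NDI 0.35, 0.40, 0.55, 0.60, 0.70; pain 0.48, 0.55, 0.65, 0.70, 0.80 (the table's bothersomeness column). Booster effect +0.20 in each group.

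**Step 1: reproduce the stated power.** For a group-stratified comparison, power = Φ[(D − 1.96·√V0)/√V1], where

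- D = Σ(p2 − p1)·n/2
- V0 = Σ p̄(1 − p̄)·n/2, with p̄ the mean of p1 and p2
- V1 = Σ[p1(1 − p1) + p2(1 − p2)]·n/4

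NDI: D = 5 × 0.20 × 8.5 = 8.5. V0 = 1.095 × 8.5 = 9.31, root 3.051. V1 = 2.09 × 4.25 = 8.88, root 2.980. Power = Φ[(8.5 − 5.980)/2.980] = Φ(0.846) = 80.1%, against 81% stated.

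Pain: the same formula gives 87.0%, against 88% stated. Group 6 would reach 0.80 + 0.20 = 1.00, so it was capped at 0.999.

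An unstratified 85 v 85 calculation gives 77.1% and 84.7%. The stated figures are therefore consistent with the group-adjusted calculation that the article describes.

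**Step 2: is week 5 a legitimate covariate?** For Booster, yes: completing the week-5 assessment is the condition for the second allocation, so the score precedes it and exists for everyone in the comparison. For Group, no: it is measured after the first randomisation and carries the dose effect.

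**Step 3: the gain over a baseline-adjusted model.** Trials were simulated with latent normal baseline, week-5 and week-12 scores and the rates above (upper cap 0.995). They were analysed by logistic regression at week 12 with Group, Booster and baseline, with and without the continuous week-5 score. There were 2,000 runs per row (4,000 for the last four). The article gives no correlations, so all are assumed. Partial r is the week 5 to week 12 correlation given baseline, (r − b²)/(1 − b²), where b is the correlation of baseline with each later score. Gains, in percentage points, are taken before rounding.

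| b | r (wk 5–12) | Partial r | NDI: baseline → + week 5 | Gain | Pain: baseline → + week 5 | Gain |
|---|---|---|---|---|---|---|
| 0.3 | 0.3 | 0.23 | 82% → 84% | 1.6 | 89% → 89% | 0.4 |
| 0.3 | 0.5 | 0.45 | 82% → 87% | 4.1 | 88% → 91% | 2.8 |
| 0.3 | 0.6 | 0.56 | 81% → 89% | 7.9 | 89% → 94% | 5.0 |
| 0.3 | 0.7 | 0.67 | 82% → 92% | 9.6 | 89% → 96% | 6.5 |
| 0.3 | 0.8 | 0.78 | 83% → 96% | 12.8 | 88% → 98% | 9.5 |
| 0.5 | 0.5 | 0.33 | 87% → 89% | 1.5 | not run | |
| 0.5 | 0.7 | 0.60 | 88% → 94% | 6.3 | not run | |
| 0.6 | 0.5 | 0.22 | 89% → 90% | 0.7 | not run | |
| 0.6 | 0.7 | 0.53 | 89% → 93% | 4.3 | not run | |

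The gain depends on what week 5 adds beyond baseline. When baseline is itself a good predictor, less is left to recover. The simulation error of a single power near 82% is about √(0.82 × 0.18/2,000) = 0.9 points.

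**Step 4: type I error.** With no booster effect and 12,000 runs, the week-5-adjusted test rejected in 5.1%, 5.3% and 5.3% of trials at r = 0.3, 0.6 and 0.8.

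**Step 5: what happens if week 5 goes into Model 2.1 itself.** With b = 0.3, the Group 6 v Group 2 log odds ratio falls from 1.86 to 1.27 at r = 0.5, and from 1.88 to 1.06 at r = 0.7. Its power falls from 0.89 to 0.50 and from 0.92 to 0.29.

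**The case against.** The strongest reply is that nothing here is wrong. The booster contrast is randomised within group, stratified by baseline NDI and tested with Group in the model, and the stated power reproduces. All of that stands. A reader might infer that leaving out week 5 biases the comparison or leaves it underpowered. The documents do not support that: chance imbalance in early response is already allowed for by the 5% test, and change from the original baseline is a coherent outcome for comparing 4 with 10 weeks of treatment.

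A reader might also infer that the plan adjusts for baseline and nothing else. It does not say so. Z is open, age and gender are given as examples, and a fuller analysis plan may list more. What can be said is that every covariate the article names predates the first randomisation.

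Nor is the change cost-free. Step 5 shows that adding week 5 to Model 2.1 would remove much of the dose effect that the model is also meant to estimate. In a logistic model, week-5 adjustment also changes the booster odds ratio from one averaged over week-5 status to one conditional on it.

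Finally, the gain rests on correlations the article does not give and may be trivial. That is a fair limit on its size.

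The point survives as more than a request for detail. The article prints one model for two randomisations, and one covariate set cannot be the best choice for both.

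**Conclusion.** The point holds as a missed efficiency gain in a valid analysis. Against a baseline-adjusted model, the week-5 score adds roughly 1 to 10 points of NDI power for week 5 to week 12 correlations of 0.3 to 0.7, and up to about 6 points for pain, with type I error near 5%. At a correlation of 0.8 the NDI gain would approach 13 points. If baseline already predicts later scores well (0.6) and the week 5 to week 12 correlation is 0.5, the gain is under 1 point.

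These figures assume Table 4 rates at week 12 without booster, a 0.20 booster effect in every group, a two-sided 5% test, latent normal scores and the correlations shown. That the score is available and precedes the booster allocation rests on the article alone; the size of the gain does not.

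**What to change.** Prespecify a separate model for the Booster effect, containing Group, Booster, the baseline score and the continuous week-5 value of the same outcome (NDI or pain). The outcome definition, change from the original baseline, need not alter. State whether the reported booster effect is conditional on week-5 status or standardised to a marginal one, for example a difference in proportions improved averaged over the re-randomised participants. Keep Model 2.1 without week 5 for the Group effects at weeks 12 and 26.

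Fix the choice before outcome data by booster arm are seen. The cost is one extra model and one sentence on the target effect; no new data are needed.

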## Discussion

Several logistical complexities are associated with this trial. Because there was little information about dosing available in the literature when this trial was designed, we used a rather broad dosing schedule, ranging from 60 to 180 min of treatment in 1, 2 or 3 weekly sessions. We anticipated that recruiting participants who are able to attend any of these dosing schedules could be challenging as could adherence in the highest doses. If necessary, such arms would be dropped. Another challenge was that persons with more mild neck pain might exaggerate their pain so that they could enter the trial. By not publicizing all entry criteria and by requiring a clinic visit before randomization, we plan to minimize these concerns.
